### Procedure and adherence to treatment

Participants who pass through the screening process will be recruited in clinics or by telephone, depending on their availability. They will be consented during clinic appointments or by mail. Each couple will be given an envelope with their study identification number (ID) and login information with which to enroll into the True NTH website. The login password is coded to randomize the participating couple into the intervention or control arm of the study. After logging in, participants will provide basic demographic information. Patients will be asked to identify the gender of their partner and type of treatment they will undergo. Once this information is entered, the couple will be sent to surveys tailored to their sexual orientation and treatment type. They will then be asked to fill out baseline surveys. The participants who are randomized into to the intervention arm will access content tailored to their treatment and sexual orientation. Participants who do not fill out their baseline surveys will receive up to 3 phone calls from the study coordinator at participating sites. Those who do not fill out baseline surveys will not be able to continue in the study. Participants who do not log into a given module will receive up to 3 email reminders which are programmed into the intervention. Participants will be allowed to move forward in the intervention even if they do not log into the 3-month surveys to enable tracking their interest in the web-based support.

Participants in the intervention arm will receive up to 3 email reminders when their successive modules become available. They will be able to continue in the intervention even if they do not access the modules. Participants in the control arm will access a link to a “Sexual Health after Cancer” web page of the American Cancer Society (ACS). They will receive 3 email reminders. The ACS website link will be available each time these participants access the True NTH website, for example when they fill out their 3 month and 6 month surveys. They can also return to the True NTH website at will throughout the time of the study. As participants will enter the study prior to treatment, their study participation will continue for approximately 7 months.

### Measures

Measurement timeline that includes both the primary measure and secondary measures is outlined in Table 2. Description of the measures is included in this section.

**Table 2 Tab2:** Study measures and data collection timeline

Variable	Measure	Assessment					
		*Baseline*		*3 Months*		*6 Months*	
		Patient	Partner	Patient	Partner	Patient	Partner
PRE-EXISTING AND CLINICAL CHARACTERISTICS							
Demographics	Demographic survey	X	X			X	X
Comorbidities	Katz Comorbidity Questionnaire Charlson Comorbidities Index	X	X			X	X
Clinical data	Medical Chart Review	X		X		X	
Patient prostate cancer related symptoms	Expanded Prostate Cancer Index Composite (EPIC)	X		X		X	
Patient expectation of sexual function	Expanded Prostate Cancer Index Composite-Exp (EPIC-Exp)	X					
Partner sexual function							
Female	Female Sexual Function Index (FSFI)		X		X		X
Male	The International Index of Erectile Function (IIEF)		X		X		X
Expectations	Expectation of Success of Treatment	X	X				
PRIMARY OUTCOME							
Global Satisfaction with Sex Life	Patient Reported Outcome Measure Information System (PROMIS) Global Sexual Satisfaction	X	X			X	X
SECONDARY OUTCOMES							
Interest in sex	PROMIS Interest in Sex Life	X	X	X	X	X	X
Sexual activity	PROMIS Sexual Activity	X	X	X	X	X	X
Resources							
Use of Aids	PROMIS Use of Aids	X	X	X	X	X	X
Knowledge	Knowledge Building Assessment	X	X	X	X		
Dyadic Coping	Dyadic Coping Inventory (DCI)	X	X			X	X
Grief	Prolonged Grief about the Loss of Sexual Function			X	X	X	X
Quality of Life	Quality of Life EQ-5D	X	X	X	X	X	X
Satisfaction with Intervention	Satisfaction with Intervention					X	X

**Patient Reported Outcome Measure Information System (PROMIS) Global Satisfaction with Sex Life** [49] measures patients’ and partners’ overall satisfaction with their sex life. Participants respond to seven items on a 5-point scale. A higher score reflects greater satisfaction (Cronbach alpha = 0.92).

**PROMIS Interest in Sex Life** [49] measures patients’ and partners’ interest in sex. Participants will respond to four items on a 5- point Likert scale. A higher score will indicate a higher level of interest (Cronbach alpha = 0.87).

**PROMIS Sexual Activity** [49] is a 13-item measure that evaluates the frequency and type of sexual activity. It is a descriptive measure.

**PROMIS Use of Aids** [49] is a 7-item measure that assesses the use of hormones, personal lubrications, medications, or devices intended to allow for or improve sexual function. These items are intended to be “stand alone” items and do not comprise a unidimensional scale.

**Knowledge Building Assessment** is an 18-item measure that was adapted from a previous study. Ten items assess knowledge about the effect of prostatectomy on erections, understanding of penile rehabilitation, erectile aids, expectations for erection recovery, flexible couple sexuality, and barriers to sexual recovery. The items are categorical variables and will be dichotomized. A summary score will be calculated.

**Expanded Prostate Cancer Index Composite-26 (EPIC)** [50] is a 26-item prostate cancer health-related quality of life (HRQOL) instrument that assesses urinary, bowel, sexual, and hormonal treatment-related symptoms of prostate cancer. Participants respond to a Likert scale. A higher score reflects higher function (Cronbach alpha = 0.93). Sexual function cut-off scores of the EPIC are: 0–33 (severe ED), 34–45 (moderate ED), 46–60 (mild/moderate ED), 61–75 (mild ED), and above 75 (no ED).

**EPIC-Exp** [50] is a measure parallel to the EPIC, but focused on expectations of functional recovery 1 year after treatment.

**Female Sexual Function Index (FSFI)** [51] is a 19-item questionnaire measure of sexual functioning in women. It assesses six domains of sexual functioning: sexual desire, arousal, lubrication, orgasm, satisfaction and pain. A total score is a sum of the domain scores. Participants respond to a Likert scale.

**Dyadic Coping Inventory (DCI)** [52] is a 16-item questionnaire that assesses stress communication and dyadic coping as perceived by (1) each partner about their own coping (what I do when I am stressed and what I do when my partner is stressed), (2) each partner’s perception of the other’s coping (what my partner does when he or she is stressed, and what my partner does when I am stressed), and (3) each partner’s view of how they cope as a couple (what we do when we are stressed as a couple). Participants respond on a Likert scale. A higher score reflects higher dyadic coping (Cronbach alpha for subscales = 0.71–0.92)*.*

**Prolonged Grief about the Loss of Sexual Function** [53] is a 22-item scale that was adapted for sexual function loss from the Prigerson’s validated measure of prolonged grief in bereavement. Participants respond to a Likert scale.

**The International Index of Erectile Function (IIEF)** [54] is a 15-item scale with subscales that measure erectile function, orgasmic function, sexual desire, intercourse satisfaction and overall satisfaction. Participants respond on a Likert scale. A higher score reflects higher sexual function. (Cronbach alpha for subscales and overall IIEF is 0.91, 0.92, 0.92, 0.77, 0.73, 0.74, respectively). As the IIEF was validated for heterosexual sex with vaginal intercourse as the expected activity, several additional items will be added for gay participants, but not included in scoring to inform about gay sexual experience.

**Expectations of Success of Treatment** [55] is a 10-item measure, adapted from a mental health measure for confidence regarding treatment for sexual dysfunction. It measures confidence in the treatment and in the outcome of the treatment. Participants respond on a Likert scale. A higher score reflects greater confidence in the success of treatment.

**Quality of Life EQ-5D** [56] is a standardized QOL instrument for use as a measure of health outcomes. It essentially consists of 2 pages – the EQ-5D descriptive system, and the EQ visual analogue scale (EQ VAS). The EQ-5D-3 L descriptive system comprises the following 5 dimensions: mobility, self-care, usual actives, pain/discomfort and anxiety/depression. Each dimension has 3 levels: no problems, some problems, extreme problems.

**Demographic/Lifestyle Data** Demographic data such as age, partnership status, race/ethnicity, household income, education, weight, height and cigarette smoking status will be sought.

**Comorbidities** [57], such as heart disease, arthritis, diabetes and others, will be collected on a self- reported basis from both the patient and partner.

**Satisfaction with Intervention** is a 10-item survey that was developed for this study by the study team and has face validity. Participants respond to a Likert scale. Individual items are summed into a total score. A higher score means higher satisfaction.

**Clinical data** will be abstracted from patients’ health records, including PSA and clinical stage of prostate cancer at diagnosis, Gleason score, comorbidities as rated per the Charlson Comorbidities Index [58], etc. For surgical patients, pathological stage, margin status (positive/negative), pathologic Gleason score and 3-month post-surgery PSA at 3 will be collected.

### Data analysis

#### Endpoints

The primary endpoint for this study will be the PROMIS Sexual Satisfaction measure at the 6-month follow-up, a multi-item validated assessment of satisfaction with sex life that was designed to have a mean of 50 and a standard deviation of 10 in the general population. Secondary endpoints will consist of the other functional and QOL measurements, comorbidities, and satisfaction assessments (Table 2).

### Analysis

The primary endpoint of PROMIS Satisfaction with Sex Life at 6 months is expected to be a continuous measurement that is normally distributed. If not, we will transform the data for this outcome to approximate normality. Since the primary outcome is measured on both patients and partners and randomization was done at the level of each dyad, we will assess the impact of the intervention using the Actor-Partner Interaction Model (APIM) [59]. The APIM is a mixed-effects linear regression model that allows us to simultaneously estimate the association of partner characteristics with partner and patient outcomes, as well as simultaneously estimate the association of patient characteristics with both outcomes. The APIM incorporates random effects to account for the correlation between patient and partner outcomes from the same dyad. Our base model will contain (1) an indicator of intervention versus control, (2) baseline PROMIS Satisfaction with Sex Life, (3) a indicator of partner versus patient, (4) interaction terms of (3) with (1) and (2), (5) a random partner effect to account for variation among partners, (6) a random patient effect to account for variation among patients, and (7) a third random effect to account for the correlation (non-independence) between outcomes measured from the same dyad. From this base model, we can assess not only the relative impact of the intervention among dyads, but also the differential impact of the intervention on partners and partners.

We can then expand our base model to include other partner characteristics and/or patient characteristics to assess whether or not these characteristics moderate or mediate the effect of the intervention for the patient and the partner. For example, we could include baseline satisfaction with sex life of the partner and the patient and see if either or both factors moderate or mediate the effect of the intervention on 6-month satisfaction with sex life. We note that because dyads were randomized to the intervention, we expect dyad level characteristics to have little effect in our model because those factors should be nearly balanced among the two treatment arms. Thus, adjustment for them is unnecessary, except to gain statistical power. The random effects will allow us to estimate the remaining variability of outcomes among partners, among patients, and the correlation of outcomes within each dyad, that is not explained by our APIM.

All secondary endpoints will be analyzed with an APIM exactly as described for the primary endpoint. It is possible that some secondary endpoints, even after transformation, will have slightly skewed distributions. However, random effect models are fairly robust to slight deviations from normality.

Along with outcome data analyses, we will conduct an analysis of the logistics of participant activity. This will include participant engagement with the modules of the intervention on the web, the need for reminders, time spent on each module and number of times each module was accessed.

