**Methods:**

The study team developed an interactive, web-based intervention, tailored to type of treatment received, relationship status (partnered/non-partnered) and sexual orientation. It consists of 10 modules, six follow the trajectory of the illness and four are theme based. They address sexual side effects, rehabilitation, psychological impacts and coaching for self-efficacy.

Each includes a video to engage participants, psychoeducation and activities completed by participants on the web. Tailored strategies for identified concerns are sent by email after each module. Six of these modules will be tested in a randomized controlled trial and compared to usual care. Men with localized prostate cancer with partners will be recruited from five academic medical centers. These couples (*N* = 140) will be assessed prior to treatment, then 3 months and 6 months after treatment. The primary outcome will be the survivors’ and partners’ Global Satisfaction with Sex Life, assessed by a Patient Reported Outcome Measure Information Systems (PROMIS) measure. Secondary outcomes will include interest in sex, sexual activity, use of sexual aids, dyadic coping, knowledge about sexual recovery, grief about the loss of sexual function, and quality of life. The impact of the intervention on the couple will be assessed using the Actor-Partner Interaction Model, a mixed-effects linear regression model able to estimate both the association of partner characteristics with partner and patient outcomes and the association of patient characteristics with both outcomes.

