## Methods

### Study setting

Recruitment will take place in urology and radiation oncology clinics at participating sites in the True NTH consortium: University of Michigan, Emory University, Johns Hopkins University, University of California –Los Angeles and Memorial Sloan Kettering Cancer Center. Sites were selected based on (1) patient volume which will impact feasibility and recruitment costs, (2) diversity of the patient population, and (3) current standard of care regarding sexual health. Each site will have a site PI and a study coordinator. The website’s survey and intervention couple engagement logistics data will be centrally managed at the University of Michigan which will also serve as the coordinating site for clinical data and a provider of technical support for all participating sites. Potential participants will be identified by a member of the study team at participating sites through screening clinic and surgical schedules as well through referral by the treating physician. The goal for each site will be to recruit a minimum of 15 couples and a maximum of 50 couples.

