### Randomization

The patient/partner dyad will be randomized to either the intervention arm or the usual care arm after completion of the informed consents, and prior to initiation of treatment. Randomization will be performed using a computer-generated randomized block design to minimize the potential for sample size differences between the two arms. The randomized block design will be stratified by enrollment site to facilitate ease of administration of the trial (Fig. 2). Participants randomized to usual care will be routed to the American Cancer Society’s web page that provides information about the sexual side-effects of cancer and sexual rehabilitation, which can be considered a part of usual care. Participants will be blinded as to the arm that they are entering by language at recruitment which will indicate that we are comparing two supportive interventions for sexual recovery after prostate cancer treatment. Participants will be unblinded by letter after they complete their 6-month survey.

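### Randomisation is stratified by enrolment site but the listed primary model has no site term: if site predicts outcome, the test is somewhat conservative and attainable power is forgone

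*Protocol article*

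**What the plan says.** On allocation, the Randomization section of the protocol article states: "The randomized block design will be stratified by enrollment site to facilitate ease of administration of the trial". Couples "will be recruited from five academic medical centers", and under Study setting the recruitment target is given as: "The goal for each site will be to recruit a minimum of 15 couples and a maximum of 50 couples".

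On analysis, the Analysis section numbers seven components of the primary model. It opens with "Our base model will contain (1) an indicator of intervention versus control, (2) baseline PROMIS Satisfaction with Sex Life", goes on to "3) a indicator of partner versus patient, (4) interaction terms of (3) with (1) and (2", adds random effects for partner and for patient, and closes with "7) a third random effect to account for the correlation (non-independence) between outcomes measured from the same dyad". None of the seven is site. The section allows the model to be expanded with partner or patient characteristics, to study moderation and mediation; site is not named there either. All secondary endpoints are to be analysed with the same model.

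On adjustment in general, the section argues that randomisation should leave dyad-level characteristics nearly balanced, and concludes: "Thus, adjustment for them is unnecessary, except to gain statistical power".

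**The concern.** Stratified blocks force the arms to be balanced within each site. Differences between sites therefore cannot move the arm comparison, so the true sampling error of the treatment estimate excludes them. A model without site does not know this. It leaves the between-site variance in its residual and dyad components and builds the standard error from them. The plan's reasoning about balance deals with bias. For a factor balanced by design, the balance is itself the reason why leaving the factor out makes the standard error too large.

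The intervention is allocated to whole dyads, so a site effect shared by both members would sit in the dyad random effect. It would also raise the within-dyad correlation that the plan intends to estimate.

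At stake are confidence intervals wider than they need be, a real type I error below the nominal 5%, and some power that the design has already made available, for the primary and all secondary endpoints. All of this is conditional on site predicting the outcome once baseline satisfaction is in the model.

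**Working it through.** **Inputs from the documents.** Power calculations: means 50 vs 45, so a difference of 5; SD 10; two-sided 5%; 128 dyads, that is 64 per arm; 80% power by t-test. Randomization: blocks within site. Study setting: five sites of 15 to 50 couples.

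**Assumed, because the documents give no figure.** A share *s* of the total outcome variance lies between sites, with *s* = 0%, 2%, 5%, 10% or 15%. The total SD is held at 10.

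**Simplification.** One outcome per dyad, two arms, no baseline covariate and no patient/partner structure. This is not the planned model.

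**Step 1: the plan's own figure.** By normal approximation, n per arm = 2 × (1.960 + 0.842)² × (10/5)² = 62.8, so 63. With 64 per arm the standard error is 10 × √(2/64) = 1.768, and the exact t-test on 126 degrees of freedom has 80.1% power. The stated 128 dyads and 80% are reproduced.

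**Step 2: standard errors.** Without site, the reported SE stays near 10 × √(2/64) = 1.768. Because allocation is balanced within site, the true SE is 10 × √(1 − s) × √(2/64). The ratio is 1/√(1 − s). For s = 10% the true SE is 1.677, and 1.768/1.677 − 1 = 5.4%.

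**Step 3: power and type I error.** Without site, the test rejects when the estimate exceeds 1.979 × 1.768 = 3.50 in absolute size, while the estimate varies with the true SE. Power is 1 − Φ((3.50 − 5)/true SE), and type I error is 2 × (1 − Φ(3.50/true SE)). With site, power comes from the t-test using the true SE and four fewer degrees of freedom (122).

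| Assumed site share | True SE | Reported SE too large by | Type I error without site | Power without site | Power with site | Difference (points) |
|---|---|---|---|---|---|---|
| 0% | 1.768 | 0% | 4.8% | 80.2% | 80.1% | −0.1 |
| 2% | 1.750 | 1.0% | 4.6% | 80.5% | 80.9% | 0.4 |
| 5% | 1.723 | 2.6% | 4.2% | 80.8% | 82.1% | 1.3 |
| 10% | 1.677 | 5.4% | 3.7% | 81.5% | 84.1% | 2.6 |
| 15% | 1.630 | 8.5% | 3.2% | 82.2% | 86.1% | 3.9 |

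The 4.8% at a zero share is an artefact of pairing a normal distribution with a t critical value; the exact figure is 5%.

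**Step 4: simulation.** Sites of 40, 32, 24, 16 and 16 dyads (128 in all, each within 15 to 50), balanced within site, five site effects drawn at random, 40,000 trials per setting:

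| Assumed site share | Power without / with site | Type I error without site |
|---|---|---|
| 0% | 80.2 / 80.2% | 5.1% |
| 2% | 80.5 / 80.9% | 4.9% |
| 5% | 80.9 / 82.1% | 4.4% |
| 10% | 82.0 / 84.0% | 4.1% |
| 15% | 82.7 / 85.9% | 3.9% |

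The differences are 0, 0.4, 1.2, 2.0 and 3.2 points. A smaller run of 4,000 trials per setting gave 2.1 points at 10% (82.5 vs 84.6%) and 3.0 points at 15% (83.3 vs 86.3%). Together with Step 3 this gives the ranges of 2 to 2.6 and 3 to 4 points.

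**Step 5: why the SE figures in Step 2 are upper values.** The formula treats the between-site variance seen in the sample as equal to the assumed share. With five unequal sites, the expected in-sample part is 1 − Σp², where p is each site's fraction of the dyads: 1 − (40² + 32² + 24² + 16² + 16²)/128² = 1 − 3712/16384 = 0.773. The average overstatement is then about √((1 − s + 0.773s)/(1 − s)) − 1. That is about 4% at s = 10% and about 7% at s = 15%, rather than 5.4% and 8.5%. This also explains why the simulated type I errors lie closer to 5% than those in Step 3.

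**The case against.** The strongest reply is that the plan has considered adjustment and declined it: balance protects validity, and adjustment only buys precision. That is correct on bias and stands. It does not name site, and it does not deal with the conservative standard error that stratified allocation produces.

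A second reply is that this is a condensed article and that stratification covariates are often settled in an analysis plan. Here, though, the article does not merely announce a mixed model. It lists the terms and carries the list to every secondary endpoint, so the model is fixed without site.

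A third reply concerns the size. The baseline score may absorb stable differences between site populations, and the calculation leaves that covariate out. This stands: the residual site share is unknown and may be close to zero. Care given at a site after treatment would act after the baseline measurement, so baseline need not absorb everything.

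Three stronger readings are tempting, and the documents do not support them:

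- A reader might infer that the sites are known to differ, because they were chosen partly on "diversity of the patient population, and (3) current standard of care regarding sexual health". These are selection criteria. The article does not say that outcomes differ by site; the diversity may lie within sites, and selecting on standard of care could make sites more alike. All controls are also sent to the same web page.
- A reader might infer that the standard error is overstated as a matter of fact. With no site effect it is not.
- A reader might infer that the 80% power is at risk. The sample size rests on an unadjusted t-test with SD 10, which as the planning SD already includes any site variance. In Steps 3 and 4, power without site stays at or slightly above plan at every assumed share.

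**Conclusion.** The point holds as one of efficiency and of consistency between design and analysis. The stratification factor is missing from a model that is otherwise listed term by term. If site predicts the 6-month score after baseline adjustment, the reported standard error is somewhat too large, type I error falls below 5% and attainable power is forgone. The treatment estimate remains unbiased and the test remains valid.

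For assumed site shares of 2% to 5% the loss is about 0.4 to 1.3 points of power. It reaches 3 to 4 points only at an assumed 15%, and at a zero share there is none. These sizes rest on the assumed shares, a total SD of 10, 64 dyads per arm, and a two-arm calculation without baseline or dyad structure. They show direction and order of magnitude, not a forecast for the planned model.

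**What to change.** Add enrolment site to the numbered base model in the Analysis section as a fixed effect with four indicators for the five sites. Because the secondary endpoints use the same model, the change carries over to them. If the trial team prefers to leave site out, the plan should say so and give the reason.

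The cost is one line of model wording and four degrees of freedom out of about 128 dyads. No new data are needed, since site is known for every couple at randomisation, and the sample size need not change. At a zero site effect the penalty is negligible: 80.2% vs 80.1% by formula, and 80.2% both ways in simulation. Naming the term in advance also removes any later choice about whether to adjust for site.

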### Participant selection

#### Inclusion criteria

Patients diagnosed with localized prostate cancer will be eligible if they are planning to receive definitive treatment within 3–6 weeks after diagnosis with either radiation or prostatectomy without ADT. Participants must be in a 6 month or longer relationship with a spouse/partner who is willing to sign an informed consent. Informed consent must be signed at least 2 weeks prior to the start of treatment so that the participants will have time to complete baseline surveys and access the first module of the intervention. Additionally, participants must be able to speak or read English without cognitive deficit, not be in acute psychiatric crisis, have reliable internet access with separate addresses for the patient and partner, and be 18 years of age or older.

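### Baseline satisfaction is offered as a possible mediator of the intervention effect; measured before the intervention, it can only be a moderator

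*Protocol article*

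**What the plan says.** The Analysis section of the protocol article defines a base model and then an optional expansion of it. The fixed terms of the base model are given as "1) an indicator of intervention versus control, (2) baseline PROMIS Satisfaction with Sex Life, (3) a indicator of partner versus patient", followed by "4) interaction terms of (3) with (1) and (2". Three random effects complete it: one for partners, one for patients and one for the dyad.

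The expansion is introduced with "We can then expand our base model to include other partner characteristics and/or patient characteristics to assess whether or not these characteristics moderate or mediate", with reference to the intervention effect. Its only worked example is that "we could include baseline satisfaction with sex life of the partner and the patient and see if either or both factors moderate or mediate", with 6-month satisfaction as the outcome.

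On timing, the Inclusion criteria ask for consent at least two weeks before treatment so that "participants will have time to complete baseline surveys and access the first module of the intervention". Under Procedure and adherence to treatment, "The login password is coded to randomize the participating couple into the intervention or control arm of the study"; couples then complete the baseline surveys, and those who do not complete them cannot continue.

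The Analysis section describes the model class as able to "simultaneously estimate the association of partner characteristics with partner and patient outcomes". The Abstract describes it in similar terms: "able to estimate both the association of partner characteristics with partner and patient outcomes".

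**The concern.** Mediation means that the intervention changes an intermediate variable, which in turn changes the outcome. A variable whose value is fixed before the intervention begins cannot take that place. It can modify the size of the effect, or it can serve as a covariate that improves precision.

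If the example were carried out as written, the arms would differ somewhat at baseline by chance. The arm coefficient would shift when baseline was added, and that shift could be reported as a mediated share. It would be a statement about how the intervention works, resting on noise. Meanwhile the data that could address mechanism, the 3-month measures in Table 2, are not mentioned in the example.

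**Working it through.** **Inputs.** From Power calculations: SD 10, expected means 50 and 45 (difference 5), 128 dyads, two-sided 5%, 80% power. Assumed, because the article does not give it: the within-arm correlation r between baseline and 6-month satisfaction, taken as 0.5 with a range of 0.3 to 0.7.

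**The plan's own figure.** The normal approximation gives n per arm = 2 × (1.960 + 0.842)² × 10² / 5² = 62.8, so 63. The exact t-test power is 79.5% at 63 per arm and 80.1% at 64 per arm. The stated 128 (64 per arm) is reproduced, and nothing below changes it.

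**True mediated effect.** The indirect effect is a × b, where a is the effect of arm on the mediator and b the effect of the mediator on the outcome given arm. Dyads are randomised and the baseline survey precedes module content, so a = 0 and a × b = 0 whatever the value of b.

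**What chance produces.** For one role (patients, or partners), with 64 per arm:

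- SE of the baseline difference between arms: 10 × √(2/64) = 1.77 points.
- With equal SDs b = r, so the SD of the spurious indirect effect at r = 0.5 is 1.77 × 0.5 = 0.88 points.
- 95% range: ±1.96 × 0.88 = ±1.73 points, which is 1.73 / 5 = 35% of the planned difference.
- At r = 0.3: ±1.96 × 1.77 × 0.3 = ±1.04 points, or 21%.
- At r = 0.7: ±1.96 × 1.77 × 0.7 = ±2.43 points, or 49%.

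A simulation of 4,000 trials (64 per arm, SD 10, effect 5, baseline slope 0.5) agrees. The mean indirect effect was −0.01 and its SD 0.89. The arm-to-baseline path was significant at 5% in 4.75% of trials, which is the nominal error rate.

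**Which measures can come between intervention and outcome (Table 2).**

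| Measure | Baseline | 3 months | 6 months | Possible use |
|---|---|---|---|---|
| Knowledge | yes | yes | no | mediator, adjusted for its own baseline |
| Interest in sex | yes | yes | yes | mediator, adjusted for its own baseline |
| Use of aids | yes | yes | yes | mediator item by item; Measures says the items form no single scale |
| Grief | no | yes | yes | mediator, adjusted for baseline satisfaction only |
| Dyadic coping | yes | no | yes | concurrent association only |

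**Terms in the base model.** If term (2) is each member's own baseline, the fixed part has 6 columns: intercept, arm, own baseline, role, role × arm and role × own baseline. The other member's baseline and its interaction with role would make 8. The random partner effect is a variance component, not a cross-partner regression effect. Term (2) does not say whose baseline it is. The expansion names the baselines of both members, which suggests own baseline only in the base model but does not settle it.

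**The case against.** The wording is permissive and the example is one of two alternatives. A reader might infer that the plan commits to a mediation test on baseline satisfaction. It does not: the expansion is optional, the example is illustrative, and its moderation half is valid. The general sentence about patient and partner characteristics is not confined to baseline variables, so mediation is not ruled out for all of them. The same paragraph also expects dyad-level factors to be nearly balanced between the arms. All of this stands, and it limits the point to the named example and to baseline characteristics generally. It does not rescue the example, because the balance argument is itself the reason why a baseline variable cannot mediate.

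A reader might also infer that the base model omits the cross-partner effect for which the APIM was chosen, and so fails the dyadic question in the Abstract. The article does not support that. The cross-partner sentences describe what the model class can do. For the base model itself the article claims only the intervention effect and its difference by role, which arm and role × arm supply. The expansion brings in the baselines of both members. Placing the other member's baseline there is a choice of staging. Because arm is a randomised dyad-level variable, leaving that term out of the base model does not bias the treatment effect.

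The absence of written-out product terms or of a mediation estimator is detail that an article may leave to the full protocol or analysis plan, and it is not held against this one.

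One might object that the baseline survey follows allocation, since the login already codes the arm. Participants are to be kept unaware of their arm, however, and the survey comes before module content, so no route from the intervention to the baseline score is apparent.

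**Conclusion.** The point holds for the mediation half of the example: the article names an analysis that cannot be valid for the variable it names. The true mediated effect is 0. At r = 0.5 a reported value could reach about a third of the planned 5-point effect by chance.

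The zero rests on randomisation, on baseline surveys being completed before module content, and on blinding to arm at that stage. The size of the noise rests on the assumed correlation and on 64 per arm with SD 10.

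The consequence is confined to an optional secondary analysis. The primary treatment effect, its difference by role and the sample size stand. The unstated ownership of term (2) is a minor matter of clarity.

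**What to change.** 1. Remove mediation from the example and from any use of baseline characteristics. Test these as moderators with arm × baseline terms, and with arm × baseline × role where the question differs between patients and partners.
2. Limit mediation to measures taken after the intervention starts and before the 6-month outcome: 3-month knowledge and interest in sex, each adjusted for its own baseline; 3-month use of aids, item by item; and 3-month grief, adjusted for baseline satisfaction because baseline grief is not collected.
3. Describe 6-month dyadic coping as a concurrent association, not as a mediator.
4. State whether term (2) is the member's own baseline only. If it is, say that cross-partner associations are estimated in the expanded model.

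The cost is a few sentences and some product terms in exploratory models. No added data collection, change in sample size or change to the primary analysis is needed.
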